### **Sample size calculation**

For the superiority primary outcome, the sample size calculation is based on an estimated 20% reduction in duration of antibiotic treatment. Assuming the mean duration of antibiotic treatment of 7 days (168 hours) and an SD of 5 days (120 hours), with an  $\alpha$  of 0.05 and a  $\beta$  of 0.1. The trial needs 262 patients in each group (524 patients in total). However, some patients may be discharged before reaching the stopping rules and these patients would not be stopped according to the CRP guidelines. We assume that 20% of patients are going to be discharged before the stopping rule was enacted or lost to follow-up. To ensure enough power for independent analysis for the three study population groups we apply this power calculation for each group. Furthermore, for children 6 months to 12 years further inflation of sample size by 50% is done to ensure exploration of sub-groups with different symptoms of infection (e.g. pneumonia, diarrhoea etc.). To establish non-inferiority of the second primary outcome of relapse of infection, assuming event rate

of 5% of relapse, non-inferiority margin of 6%, one-sided alpha of 2.5%, power of 90% the sample size is 278 per group i.e. total 556 children plus 20% loss to follow-up equaling 646 children.

Hence, the study aims to include 646 neonates at risk of infection, 646 neonates with suspected infection and 969 children aged 6 months to 12 years with infection - an overall total of 2261 children included. Power calculations were performed using sample size calculators provided by Sealed Envelope (21).

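### The enrolment target of 646 is not 556 plus 20% loss; at 20% loss it gives each neonatal group about 88% non-inferiority power, not 90%

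*Protocol*

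**What the plan says.** The Protocol names two primary outcomes under Study endpoints: duration of antibiotic treatment, tested for superiority, and relapse of infection, added as a safeguard in case antibiotic use falls. Sample size calculation treats both and applies the calculation separately to each of the three populations.

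For relapse it assumes a 5% event rate, a 6% margin and a one-sided alpha of 2.5%, and concludes "power of 90% the sample size is 278 per group", or 556 in total. It then adds the allowance for loss: "i.e. total 556 children plus 20% loss to follow-up equaling 646 children".

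The recruitment targets follow from that figure: "646 neonates at risk of infection, 646 neonates with suspected infection and 969 children aged 6 months to 12 years", 2261 overall. The children's target is 646 raised by a further 50% for sub-group exploration. No loss rate other than 20% appears in the document.

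**The concern.** The sentence states an equation that is false under both usual ways of allowing for loss. It cannot be put down to rounding, since 646 is 21 below one answer and 49 below the other. Nor does it look like a damaged digit: 646 is used again in the same section, and both 969 and 2261 are built on it.

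Relapse has the larger stated requirement before loss (556, against 524 for duration), so it should set the size of each population. If its allowance for loss is miscalculated, the 90% power claimed for the safety-related primary outcome is not supported at the loss rate the Protocol itself plans for. The figures in this sentence are also the ones against which recruitment and the final report will be checked.

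**Working it through.** **Inputs**, all from Sample size calculation unless noted:
- relapse rate 5%, taken as equal in both arms (the text does not say so, but this reproduces 278)
- non-inferiority margin 6 percentage points, absolute
- one-sided alpha 0.025, power 90%
- 1:1 allocation (Randomisation and blinding)
- loss to follow-up 20%, assumed equal in the two arms

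**Step 1. Reproduce the size before loss.**

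n per arm = (1.960 + 1.282)² × 2 × 0.05 × 0.95 / 0.06² = 10.507 × 0.095 / 0.0036 = 277.3, rounded up to 278; total 556. This agrees with the Protocol.

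**Step 2. Apply the allowance for loss.**
- Mark-up: 556 × 1.20 = 667.2
- Division by the retained fraction: 556 / 0.80 = 695
- Stated: 646

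Working back, 646 / 556 = 1.162, a mark-up of 16.2%. The loss that 646 can absorb while keeping 556 is 1 − 556/646 = 13.9%.

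**Step 3. Power delivered.** With n evaluable per arm,

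power = Φ( 0.06 / √(2 × 0.05 × 0.95 / n) − 1.96 ).

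At 646 with 20% loss, 646 × 0.8 = 516.8 evaluable, about 258 per arm:

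0.06 / √(0.095 / 258) − 1.96 = 3.127 − 1.960 = 1.167, and Φ(1.167) = 0.878.

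| Enrolled | Loss | Evaluable | Non-inferiority power |
|---|---|---|---|
| 646 | 20% | 517 | 87.8% (258 per arm) |
| 646 | 13.9% | 556 | 90.1% |
| 646 | none | 646 | 93.8% |
| 667 | 20% | 534 | 88.9% |
| 696 | 20% | 557 | 90.1% |
| 969 (children) | 20% | 775 | 96.9% |

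**Step 4. What depends on 646.** 646 × 1.5 = 969, and 646 + 646 + 969 = 2261. The totals are internally consistent, so the fault lies only in the step from 556 to 646.

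**The case against.** The strongest reply is that the effect is small. Power falls from 90% to about 88%, only if loss reaches the full 20%, and only in the two neonatal groups. With loss of 13.9% or less the stated power holds. If 667 is taken as the intended figure, 646 is 21 short and costs about one percentage point. All of this stands, and it limits how serious the point is. It does not make the equation true.

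A reader might go further in three directions that the document does not support.

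- **Superiority power is also below 90%, at 89%.** That figure treats all of the 20% as missing. The Protocol's 20% for the duration outcome mixes losses with patients discharged before the stopping rule applies, and Data analysis follows intention to treat, so early discharges stay in and dilute the effect. If, as an extreme assumption, all 20% were early discharges with no effect, the difference would fall from 1.4 to 1.12 days, and 323 per arm would give about 81%. The split is not stated, so the range is about 81% to 89%, and no single figure can be put into the text.
- **The stated 262 per group for superiority is wrong.** An exact 33.6-hour difference gives 269, but 262 reproduces if the difference is rounded to 34 hours: 2 × 120² × 10.507 / 34² = 261.8. That is a rounding matter, separate from this point.
- **646 was carried over from the superiority calculation.** 538 × 1.2 = 645.6, but 538 appears nowhere in the Protocol. The stated 524 gives 629 (× 1.2) or 655 (/ 0.8). The origin of 646 is unknown.

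**Conclusion.** The point holds in a limited form. The Protocol's statement that 556 plus 20% equals 646 is wrong under either convention. At the planned 20% loss, each neonatal group has about 88% power for non-inferiority on relapse, a shortfall of about two percentage points from the stated 90%. The children's comparison as a whole is unaffected at about 97%, although the extra 50% there was meant for sub-groups.

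This rests on equal true relapse rates of 5%, an absolute 6-point margin, a normal approximation and equal loss in the two arms. The first, second and third of these reproduce the Protocol's own 278.

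It would be too strong to infer that the trial is seriously underpowered or that enrolment has to rise: 646 gives 90% whenever loss is at most about 14%. The text should be corrected because a false equation underlies every enrolment target, and the correction is cheap.

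**What to change.** Keep the targets of 646, 646 and 969, correct the equation, and restate the power. Suggested wording:

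*The non-inferiority calculation requires 278 evaluable children per group (556 in total) for 90% power. Enrolling 646 per neonatal group gives about 88% power for non-inferiority at 20% loss to follow-up, and 90% if loss is at most 14%.*

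This costs one text change and a stated power about two points lower. It needs no extra patients and changes neither the design nor the analysis.

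If the sponsor prefers to keep 90% power at 20% loss, the neonatal target has to be 695, or 696 for equal arms. At 696 that is 50 more per neonatal group, 100 in all. If the children's target were also rebuilt as 1.5 times the base, it would become 1044 and the total 696 + 696 + 1044 = 2436, against 2261 now. A target of 667 should not be adopted as the remedy, because it leaves power at 88.9% after 20% loss.

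If a loss rate other than 20% was intended, the sponsor should state it, so that 556, the loss rate and 646 agree.

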### **Randomisation and blinding**

We plan not to use the cluster randomization because it is not possible in the Zanzibar setting due to the limited number of sites (two) while cluster randomization requires a large number of sites that are relatively comparable. Furthermore, the current study in Kirgizstan has shown that individual randomization is feasible and can be applicable in Zanzibar (22). The randomisation will be carried out by a responsible Research Assistant through the Sealed Envelope™ programme ([www.sealedenvelope.com](http://www.sealedenvelope.com)). This person will inform the HCW directly of the result of the randomization. Follow-up will be blinded as well. Participants will be randomised (1:1) to either standard care or care according to CRP POCT. Randomisation will be stratified by male/female as well as within the three study groups.

### **Study procedures**

Participants are screened for eligibility at the participating hospitals by a research assistant (RA) prior to routine examination by a clinician. Parents /caregivers of eligible children are requested for informed consent, after having received oral and written information regarding the trial. Participants are then randomized to the intervention group (CRP POCT) or control group (usual care) by a responsible RA through the REDCap Randomization Module (23). Case report forms (CRFs) are filled out by RA for all participants at the first consultation and every subsequent day the participant is admitted. Participants assigned to the intervention group are provided with CRP POCT during consultation with their clinician at admittance and after 18-24 hours of treatment. The CRP POCT is carried out as a prick test using capillary blood. Children in the control group do not have the CRP POC test taken. Decision on the treatment of participants is exclusively the responsibility of the clinicians of the included hospitals. To assess adherence, all treatment decisions including deviations from CRP recommendations are recorded in case report forms (CRFs). Reasons for deviation are documented for transparency and allow for subgroup analysis.

During admission RA follow the enrolled children daily and register

- Demographic details including sex, age, co-morbidities
- Obstetric and neonatal background information
- Duration of clinical symptoms prior to consulting
- Presence of specific and general symptoms
- Clinical assessments and results of clinical examination (oxygen saturation, respiratory rate, blood pressure, heart rate, body temperature)
- All diagnostic tests performed or ordered
- Management: antibiotic, antiviral prescription, other (symptomatic) medication prescribed and advised
- Additional advice: preventive measures for themselves and their family members, time-off, home isolation, hygienic measures
- Referral to other hospitals

Furthermore, HCWs in participating hospitals answer a questionnaire on professional education as well as acceptability of CRP POCT testing during the feasibility study.

### **Follow-up by phone**

After discharge from the hospital, all participants are contacted on the 7th and 28th day by phone calls from a RA who is blinded to the group allocation. Information gathered on the follow-up call includes general medical history of the child post discharge, additional diagnostic testing (with pictures of medical records or clinical follow-up if possible), complications (such as hospitalization, days in hospital, ICU stay, medication/oxygen/ventilation received, pneumonia, or death), and any medicine bought over-the-counter or prescribed by other healthcare workers (including the name of the drug, route of administration, frequency of administration and dose).

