## **Methodology**

### **Study design**

This study is a prospective open-label, individual randomised controlled clinical trial with 28 days blinded follow-up conducted in Vitongoji (VT) hospital and Mnazi Mmoja Hospital (MMH) in Zanzibar. Neonates at risk of early onset sepsis, admitted neonates (0-28 days) with clinical signs of sepsis and admitted children (6 months to 12 years) with febrile illness or diarrhoea that are eligible for participation and parents will be asked for informed consent. If informed consent is obtained the child will undergo randomization to intervention: CRP POCT measurement at 18-24 hours of life (at risk of early onset sepsis neonates) or CRP POCT at admittance and after 18-24 hours of treatment. Further treatment and discontinuation of antibiotics will be guided by flowcharts supporting the clinicians decision of treatment, please refer to description of intervention for further details. Participants will be randomly assigned (1:1) to either CRP-guided or standard-of-care antibiotic continuation/discontinuation. Both groups will be followed up by telephone up to 28 days after intervention. The principal investigator will not be aware of the results of the randomisation and follow-up will be blinded as well. CRP-level and treatment data will be recorded and entered in a central database.

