### **Study endpoints**

The primary study outcome is the duration of antibiotic treatment (number in 24-hour periods between start and end of antibiotic treatment) within 14 days of the admittance of included neonates and children in each study arm (superiority analysis). Antibiotic use during admittance and a composite measure of antibiotic use during admittance and discharge are reported. For every participant, the types and quantity of antibiotics given during the study period will be assessed based on individual drug administration records. To ensure patient safety in case of reduction in antibiotic use a second primary outcome relapse of infection is measured as reinstitution of antibiotics within 72 h after completion of the initial course of antibiotic treatment.

The secondary study outcomes are:

1. Antibiotic use (prescribed daily doses)
2. Choice of antibiotic drug and dose compared to local standard treatment guidelines
3. Number of days admitted in hospital
4. Number of days until resolution of symptoms
5. Development of clinical signs of sepsis
6. Proportion of cases with blood cultures collected before antibiotic treatment
7. Bacterial pathogens and AST in blood cultures
8. Hospital re-admittance within 14 days
9. Mortality at follow up day 7 and 28

Our definition of prescribed and defined daily doses accords with the recommendations of WHO. The route of administration will be incorporated in the daily dose calculations.

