### **Data collection tools**

The data collection materials will consist of:

- Informed consent (English and Swahili), appendix 2.1, will be asked by the research assistants.
- Description of available drugs, equipment for treatment such as peripheral venous catheters, i.v. fluids. This will be performed two times during the study, at initiation and end of data collection. The data will be collected by a research assistant. The content for available material is shown in appendix 2.2.
- Inclusion and eligibility assessment for neonates and children respectively, appendix 2.3 and 2.4. The risk factors according to the WHO's guidelines for neonatal sepsis and the use of prophylactic antibiotic will be assessed using a picture of the partogram, the delivery book, the antenatal card and the case file. The admitted neonates and children eligible assessment will be done by case files and admittance books.

- After inclusion the caregiver assisted by the research assistant will complete a questionnaire (English and Swahili) on socio-economic background and health seeking behaviour, appendix 2.5.
- CRP will be taken by the clinician responsible for treatment supported by the research assistant responsible for randomisation and data collection. Clinical data and treatment registration will also include the general examination, respiratory count, temperature, and a blood glucose measurement (capillary point-of-care test) and prescriptions. Emphasis will be put on the use of antibiotics during admission and status of child obtained from the hospital files, appendix 2.6.
- At the time of discharge or death a discharge form will be filled, appendix 2.7. The family will be contacted to enquire about the status of the child after discharge at day 7 and 28 primary by phone, but if not available by home visit of the research assistant, appendix 2.8.
- Questionnaire for the health care worker on their education, work experience and acceptability of using CRP will be conducted at the feasibility phase of the study using a semi-structured questionnaire, appendix 2.9.

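### The day-7 and day-28 contacts, and the mortality outcome tied to them, have conflicting time origins; counted from discharge, mortality is read at a time since randomisation that varies with length of stay

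*Protocol*

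**What the plan says.** Four sections of the protocol bear on when follow-up is counted from.

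- *Study design* describes an "individual randomised controlled clinical trial with 28 days blinded follow-up" and then states "Both groups will be followed up by telephone up to 28 days after intervention". The origin here is the intervention.
- *Follow-up by phone* states "After discharge from the hospital, all participants are contacted on the" seventh and twenty-eighth day.
- *Data collection tools* states "The family will be contacted to enquire about the status of the child after discharge at day 7 and 28".
- *Study endpoints* lists "Mortality at follow up day 7 and 28" and "Hospital re-admittance within 14 days" as secondary outcomes, neither with an origin. The primary outcome does have one: antibiotic duration is counted "within 14 days of the admittance of included neonates and children in each study arm".

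Two further facts matter. *Study procedures* says that control children are not given the CRP test. *Study endpoints* also lists the number of days in hospital as a secondary outcome, so length of stay is itself something the trial compares between arms.

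**The concern.** The sections do not agree on day 0, and neither origin on offer works for every child. The intervention is a test that control children never have. Discharge does not exist for a child who dies on the ward, yet that death must count in the mortality outcome. If the contacts are instead meant as study days, a child still admitted on day 7 cannot be phoned after discharge on that day. Two teams following this text could compute different mortality figures from the same children.

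Discharge is also a poor origin on statistical grounds. It comes after randomisation and may be affected by the allocated strategy. If one arm goes home sooner, a time point fixed relative to discharge observes that arm for less time since randomisation, and its mortality looks lower for that reason alone. Mortality is one of the outcomes a reader will use to judge whether reduced antibiotic use is safe, so the comparison should not depend on how long children stayed.

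**Working it through.** The protocol states no figure on this point that could be reproduced. The check is of the wording, followed by an illustration.

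**Inputs**

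- Origins: as set out in the four sections above.
- Length of stay L: not given in the protocol. Assumed 1 to 14 days.
- Stay by arm: not given. Assumed 7 versus 5.6 days, with 5 versus 4 and 3 versus 2 as alternatives. The first pair applies a 20% fall to 7 days (7 × 0.8 = 5.6). Those two figures are the protocol's assumptions for antibiotic duration (*Sample size calculation*), borrowed here for scale only.
- 28-day mortality risk r: not given. Assumed 2%, 5% and 10%.
- The same constant hazard in both arms, and randomisation on the day of admission.

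**Step 1: when the calls fall under the discharge reading.** Call 1 is on day L + 7 and call 2 on day L + 28 after admission.

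| Stay L (days) | Call 1 | Call 2 |
|---|---|---|
| 1 | 8 | 29 |
| 3 | 10 | 31 |
| 7 | 14 | 35 |
| 14 | 21 | 42 |

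Day-28 status is therefore read anywhere from day 29 to day 42.

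**Step 2: relative time at risk, stays of 7 versus 5.6 days.** At call 1: (5.6 + 7)/(7 + 7) = 12.6/14 = 0.90. At call 2: (5.6 + 28)/(7 + 28) = 33.6/35 = 0.96.

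**Step 3: spurious mortality difference.** Hazard h = −ln(1 − r)/28; risk by day t = 1 − exp(−h·t). For r = 5%, h = 0.05129/28 = 0.001832. By day 35 the risk is 1 − exp(−0.0641) = 6.21%; by day 33.6 it is 1 − exp(−0.0616) = 5.97%.

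| Assumed 28-day risk | Call 1: 7 vs 5.6 days' stay | Call 2: 7 vs 5.6 days' stay | Difference at call 2 |
|---|---|---|---|
| 2% | 1.01% vs 0.91% | 2.49% vs 2.40% | 0.10 points |
| 5% | 2.53% vs 2.28% | 6.21% vs 5.97% | 0.24 points |
| 10% | 5.13% vs 4.63% | 12.34% vs 11.88% | 0.46 points |

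The spurious risk ratio at call 1 is about 0.90. With stays of 5 versus 4 or 3 versus 2 days, the difference at call 2 is 0.07 to 0.34 points.

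**Step 4: re-admittance.** Counted from discharge, every discharged child has 14 days at risk. Counted from admission, a stay of L days leaves 14 − L: 13 days for a 1-day stay, 4 for a 10-day stay, none for a 14-day stay. Here discharge is the sounder origin, and the fault is only that none is stated.

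**Step 5: the 14-day antibiotic window.** Call 2 falls after day 14 under either reading, so the window is covered. Under the discharge reading, what varies is how much of the window is left to call 2: 14 − (L + 7), which is 6 days for a 1-day stay, 4 for a 3-day stay and 0 for 7 days or more. The gap from day 14 back from call 2 is L + 14, or 15 to 28 days.

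**The case against.** The strongest reply is that this is a wording problem with little numerical consequence. *Follow-up by phone* and *Data collection tools* never say outright that the days are counted from discharge. Read with *Study design*, they could mean study days 7 and 28, with phone contact for children already at home. That reading is possible but less natural, and the existence of two readings is the fault.

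It can also be said that a form is completed at discharge or death and that the calls ask about death, so fixed-time mortality could be derived later if dates are recorded. The contents of the follow-up form are not shown, so no gap in the date fields can be asserted. This supports the low cost of the fix; it does not remove the conflict over what the named outcome is. It is also true that the outcome the protocol assigns to safety is relapse, the second primary outcome, which is not tied to discharge. Mortality is the last of nine secondary outcomes.

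Three stronger readings are tempting, and the document does not support them.

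- A reader might infer that the trial expects shorter stays and so builds in a bias favouring CRP. *Hypothesis* and *Sample size calculation* expect antibiotic use and duration to fall. They say nothing of stay, which is only listed as an outcome.
- A reader might infer that the primary antibiotic outcome depends on length of stay. Its window is fixed from admittance and covered by the second call; only recall of post-discharge use varies.
- A reader might want every outcome counted from randomisation. For re-admittance that would create the dependence on stay that one wishes to avoid.

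**Conclusion.** The point holds as a conflict of time origin that affects mortality. *Study design* counts from an intervention that controls do not have. Two other sections most naturally count from discharge, and the mortality outcome takes over whichever is meant. Under the discharge reading, mortality is assessed at unequal times since randomisation, and ward deaths have no day 0.

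Any resulting bias is conditional on stay differing between arms, and its size rests wholly on assumed stays, assumed risks and a constant hazard. With those it is about 0.1 to 0.5 percentage points at the second call. If deaths cluster early in the illness, the extra days at the end of follow-up add less than this. It is small and avoidable, and worth correcting because mortality informs the safety judgement. For re-admittance the finding is limited to the missing origin.

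**What to change.** 1. Reconcile *Study design*, *Study endpoints*, *Follow-up by phone* and *Data collection tools* on one stated origin for the contacts.
2. Define mortality as death by day 7 and by day 28 from randomisation, counting in-hospital deaths, with dates of death taken from ward, discharge and call forms.
3. Keep the last call on or after day 28 from randomisation. A call 28 days after discharge already meets this for every child, because discharge follows randomisation, so the calls need not move.
4. State the origin of the 14-day re-admittance window; discharge is acceptable.
5. Leave the primary antibiotic window as it is. Moving the calls to days 7 and 28 from randomisation would make recall uniform between arms but no more complete: days 8 to 14 would be left to the last call for every child, against days 11 to 14 for a child discharged on day 3 under the discharge reading.

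The cost is protocol wording and a check that the forms capture the date of death. Sample size and number of calls do not change.
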